### Secondary, Exploratory, and Safety Endpoints

Secondary endpoints include grip strength, as measured using a vigorimeter (left/right); the Rasch-built Overall Disability Scale; Medical Research Council sum score; median, ulnar, tibial, and peroneal motor nerve conduction studies, including motor nerve conduction velocity and distal and proximal latency, amplitude, and duration of the compound muscle action potential after distal and proximal stimulation; protein levels in the cerebrospinal fluid; B cell (CD19-positive and CD20-positive) counts and T-cell (CD3-positive, CD4-positive, and CD8-positive) counts; expression of human anti-chimeric antibodies; and serum rituximab level.

The exploratory endpoints include serum antibody titers of IgG4, serum antibody titers of anti-CNTN1 and anti-NF155 IgG subclasses, and serum neurofilament level.

The safety endpoints include adverse events and vital signs and laboratory tests.

### Sample Size

The trial includes patients with CIDP that is refractory to both IVIg and corticosteroids or patients who are unable to receive or continue these therapies. Most eligible patients would be unlikely to achieve an improvement of ≥1 point on the adjusted INCAT Disability Scale even if conventional therapies were continued. An immunosuppressant (eg, cyclophosphamide, azathioprine, or cyclosporine) is generally considered to be an effective second-line treatment in about 30% of patients with refractory CIDP [19]. However, no superiority has been demonstrated for any specific agent, and no immunosuppressant is approved for CIDP in Japan. Currently, no feasible treatment approach can be recommended for patients enrolled in this study. Therefore, the threshold effectiveness rate for the proportion of patients achieving the primary endpoint of ≥1 point improvement in the adjusted INCAT Disability Scale score was conservatively assumed to be 15%, and the clinically expected effectiveness rate was assumed to be 60% in patients with IgG4 autoantibody–positive CIDP in the rituximab group. Using two-sided testing with *P*<0.05 regarded as statistically significant, we estimated that 8 cases would be needed to achieve 80% power. Accordingly, 10 patients with IgG4 autoantibody–positive CIDP will be enrolled for the rituximab group, allowing for a 20% dropout rate.

The PMDA suggested inclusion of a placebo control group for the patients who are IgG4 autoantibody–positive. We agreed to include a placebo group of 5 patients for reference purposes rather than for strict statistical comparison, given the rarity of CIDP and feasibility considerations. The placebo group has been designated as a reference group to confirm that the estimated values do not deviate markedly from the defined thresholds. Patients with IgG4 autoantibody–negative CIDP are included in another reference group to compare their response to rituximab treatment with that of patients with IgG4 autoantibody–positive CIDP. This reference group will consist of 10 patients, which is the same as the number of patients with IgG4 autoantibody–positive CIDP.

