### Statistical Analysis

All statistical analyses will be performed on an intention-to-treat basis. The primary analysis will compare the adjusted INCAT Disability Scale scores recorded before treatment (at enrollment) with those recorded at 26, 38, or 52 weeks after the start of treatment. We will calculate the proportion and 95% CI of IgG4 autoantibody–positive patients in the rituximab group who achieve an improvement of ≥1 point at any of evaluation point after 26 weeks, from baseline. The 95% CI will be calculated using the Clopper-Pearson method. Continuous variables will be analyzed using descriptive statistics, and categorical variables will be calculated as the frequency and proportion. All statistical analyses will be performed using SAS version 9.4 (SAS Institute Inc, Cary, NC). All statistical tests will be two-sided. *P* values <0.05 will be considered statistically significant.

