## Results

### Ethics Approval, Trial Registration, and Current Enrollment Status

The study protocol complies with the Declaration of Helsinki [38] and the Pharmaceutical Affairs Act in Japan. This protocol was also approved by the institutional review boards at the following sites: Nagoya University Hospital (No. 302010), Chiba University Hospital (No. 030033), Yamaguchi University Hospital (No. 201901), and Kyushu University Hospital (No. 2018312).

The necessary information for the RECIPE trial has been uploaded to ClinicalTrials.gov (NCT03864185, registered March 6, 2019) and the Japan Registry of Clinical Trials (jRC2041180037, registered January 31, 2019).

The first patient completed registration in April 2019 and received an investigational treatment in May 2019. Recruitment of patients for the RECIPE trial is ongoing at the four participating hospitals. As of January 2020, 14 cases have been enrolled. The targeted accrual is 25 cases for the full analysis set. Enrollment will close in September 2020, and the study is scheduled to end in December 2021.

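### The 20% dropout allowance does not match the intention-to-treat analysis: with two dropouts kept among 10, power lies between about 59% and 83%, depending on how they count

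*Protocol article*

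**What the plan says.** The Sample Size section of the protocol article sets up a single-arm comparison with a fixed rate. The threshold "was conservatively assumed to be 15" percent, and "the clinically expected effectiveness rate was assumed to be 60% in patients with IgG4" autoantibody-positive disease on rituximab. The test is two-sided at 0.05. On that basis "we estimated that 8 cases would be needed to achieve 80% power", and so 10 such patients "will be enrolled for the rituximab group, allowing for a 20% dropout rate".

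The Statistical Analysis section then says: "All statistical analyses will be performed on an intention-to-treat basis". It reports the proportion of antibody-positive rituximab patients who improve by at least 1 point at an evaluation from week 26 on, with a Clopper-Pearson 95% interval. It adds "All statistical tests will be two-sided" and that P "values <0.05 will be considered statistically significant".

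The enrolment status paragraph says: "The targeted accrual is 25 cases for the full analysis set". That is 10 + 5 + 10, the whole planned enrolment. Table 1 has a combined visit for week 52 or withdrawal, at which the adjusted INCAT score is recorded.

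**The concern.** Going from 8 to 10 protects power only if dropouts leave the denominator. Under intention to treat they stay in it. The two extra patients then do two things: they raise the number of responders needed, and, if they are the ones who drop out, they may contribute none.

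This bears on the only hypothesis for which the article gives a power. It also leaves one plausible result ambiguous. If 4 of 8 completers respond and the two dropouts do not, the criterion behind the sample size is met (4/8), but the analysis on all 10 fails (4/10). Which of the two counts should be settled before the data are seen, more so because the Discussion describes the study as meant to support approval in Japan.

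**Working it through.** **Inputs.** From Sample Size: threshold p0 = 0.15, expected rate p1 = 0.60, 8 analysed, 20% dropout, 10 enrolled. From Statistical Analysis: two-sided 0.05, Clopper-Pearson interval, intention to treat.

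**Success rule.** The smallest r with P(Bin(n, 0.15) ≥ r) ≤ 0.025. This is the same as a Clopper-Pearson 95% lower limit above 15%. Power is P(Bin(n, 0.60) ≥ r).

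**Step 1: the plan's own figure.**
- n = 8: r = 4 (upper tail 0.0214; lower limit for 4/8 is 15.7%); power 0.826.
- n = 7: r = 4; power 0.710. So 8 is the smallest n that reaches 80%.
- 8/(1 − 0.20) = 10.

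Both stated numbers reproduce, with dropouts taken out of the analysis.

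**Step 2: all 10 in the denominator.**
- 4/10: upper tail 0.04997, lower limit 12.2%, so it fails.
- 5/10: upper tail 0.0099, lower limit 18.7%, so it passes.

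The bar is 5. With no dropout, power is P(Bin(10, 0.60) ≥ 5) = 0.834.

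**Step 3: two dropouts kept in the denominator.** Let X ~ Bin(8, 0.60) be the responders among the 8 completers, and q the chance that each dropout counts as a responder. At least 5 responders are needed in total:

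Power(q) = P(X ≥ 5) + P(X = 4)·[1 − (1 − q)²] + P(X = 3)·q²

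with P(X ≥ 5) = 0.5941, P(X = 4) = 70 × 0.6⁴ × 0.4⁴ = 0.2322, and P(X = 3) = 56 × 0.6³ × 0.4⁵ = 0.1239.

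| q | Power |
|---|---|
| 0 | 59.4% |
| 0.15 | 66.1% |
| 0.30 | 72.4% |
| 0.45 | 78.1% |
| 0.60 | 83.4% |

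At q = 0.50 the formula gives 0.5941 + 0.2322 × 0.75 + 0.1239 × 0.25 = 0.799, so 80% is reached just above q = 0.50.

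**Step 4: variants.**
- One dropout counted as a non-responder: P(Bin(9, 0.60) ≥ 5) = 0.733.
- Each of the 10 drops out with probability 0.20 and then counts as a failure: response rate 0.60 × 0.80 = 0.48, and P(Bin(10, 0.48) ≥ 5) = 0.573.
- Dropouts excluded, against the intention-to-treat statement: 0.834 at n = 10, 0.733 at n = 9 (where r is already 5), 0.826 at n = 8, 0.710 at n = 7. Averaged over Bin(10, 0.20) dropouts, power is 0.739.

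**The case against.** The strongest reply is that the sample-size sentence is correct and the low power figure needs assumptions that the article does not make. Much of this stands.

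- **The calculation for 8 is right.** A reader might infer that the sample-size arithmetic is wrong. It is not; Step 1 reproduces it.
- **Dropouts need not be early or count as failures.** A reader might infer that the trial has 59% power. That requires both dropouts to have no score from week 26 on and to be counted as non-responders. The article says neither. Follow-up runs 52 weeks, and a patient who leaves after week 26 may already have responded. The classification rule may stand in an analysis plan that is not shown, so its absence here is no fault. The withdrawal visit helps less: the endpoint names weeks 26, 38 and 52, and nothing says that an earlier withdrawal score counts.
- **The 60% may already be a rate among all treated patients.** Power with 10 is then 83.4%. But on that reading no dropout inflation would be needed, and the plan applies one.
- **The accrual target does not define the full analysis set.** True. The denominator of 10 rests mainly on the intention-to-treat statement; the accrual target only agrees with it.
- **Another exact test would accept 4/10.** A two-sided exact test that orders outcomes by likelihood gives P = 0.04997 at 4/10. The bar is then 4, and power with two failures is 82.6%. The article does not say in so many words that success is judged by the interval's lower limit. But Clopper-Pearson is the only method it names for the primary proportion, and under it 4/10 fails.

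What the reply does not remove is the mismatch itself. The sample size drops the dropouts and the analysis keeps them.

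**Conclusion.** The point holds as an inconsistency between the dropout allowance and the analysis population. Enrolling 10 does not in general preserve 80% power at 20% dropout. Under intention to treat the bar moves from 4/8 to 5/10, and two dropouts bring power to somewhere from 59% to 83%. The stated 80% survives only if dropouts succeed nearly as often as completers (just above 50% against 60%). Excluding dropouts is no general rescue either, since power meets 80% at exactly 8 or 10 evaluable patients but not at 9 or 7.

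This rests on three readings: intention to treat means all 10 randomised to rituximab are in the denominator; success means a Clopper-Pearson lower limit above 15%; and 60% is the rate among patients who stay. The upper-tail error at 5/10 is 0.0099, so false-positive control is not at issue. Nor do the documents support concluding that the trial is too small: with no dropout, 10 patients give 83.4%.

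**What to change.** In the Sample Size section:

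1. State that the primary denominator is all IgG4-positive patients randomised to rituximab.
2. State the success rule as a Clopper-Pearson 95% lower limit above 15%, which means at least 5 of 10.
3. Replace the implication that 10 enrolled keeps 80% power at 20% dropout with: power at a true rate of 60% is 83% with no dropout and, if patients with no score from week 26 on count as non-responders, 73% with one such patient and 59% with two.

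The analysis plan should use the same denominator and the same classification rule, settled before unblinding. The change is wording only; it adds no patients, visits or procedures. The cost is a less favourable stated power.

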### Statistical Analysis

All statistical analyses will be performed on an intention-to-treat basis. The primary analysis will compare the adjusted INCAT Disability Scale scores recorded before treatment (at enrollment) with those recorded at 26, 38, or 52 weeks after the start of treatment. We will calculate the proportion and 95% CI of IgG4 autoantibody–positive patients in the rituximab group who achieve an improvement of ≥1 point at any of evaluation point after 26 weeks, from baseline. The 95% CI will be calculated using the Clopper-Pearson method. Continuous variables will be analyzed using descriptive statistics, and categorical variables will be calculated as the frequency and proportion. All statistical analyses will be performed using SAS version 9.4 (SAS Institute Inc, Cary, NC). All statistical tests will be two-sided. *P* values <0.05 will be considered statistically significant.

### Monitoring and Auditing

Monitoring and auditing will include systematic independent examination according to the study protocol, applicable regulatory requirements, and standard operating procedures.

## Results

### Ethics Approval, Trial Registration, and Current Enrollment Status

The study protocol complies with the Declaration of Helsinki [38] and the Pharmaceutical Affairs Act in Japan. This protocol was also approved by the institutional review boards at the following sites: Nagoya University Hospital (No. 302010), Chiba University Hospital (No. 030033), Yamaguchi University Hospital (No. 201901), and Kyushu University Hospital (No. 2018312).

The necessary information for the RECIPE trial has been uploaded to ClinicalTrials.gov (NCT03864185, registered March 6, 2019) and the Japan Registry of Clinical Trials (jRC2041180037, registered January 31, 2019).

The first patient completed registration in April 2019 and received an investigational treatment in May 2019. Recruitment of patients for the RECIPE trial is ongoing at the four participating hospitals. As of January 2020, 14 cases have been enrolled. The targeted accrual is 25 cases for the full analysis set. Enrollment will close in September 2020, and the study is scheduled to end in December 2021.

## Discussion

### Overview

There have been some reports on the epidemiology of IgG4 antibody–positive CIDP [14,16,17]. This phenotypic subtype presents as subacute or slowly progressive disease. The initial disability tends to be distal acquired demyelinating symmetric neuropathy, which sometimes progresses to the typical CIDP phenotype. IgG4 antibody–positive CIDP is also characterized by gait disturbance with sensory ataxia and fine tremor of the hands. The protein level in cerebrospinal fluid is markedly higher in IgG4 antibody–positive CIDP than in typical CIDP. Furthermore, a relatively large proportion of patients with antibody–positive CIDP present at a younger age. However, they are resistant to conventional therapies, such as IVIg and corticosteroids. Therefore, new therapies that can inhibit production of pathogenic antibodies in the long term are essential.

Rituximab can be expected to be effective in cases of refractory CIDP [19-32]. Some of the phenotypic characteristics, for example onset time, are different from those in anti-CNTN1–positive patients and anti-NF155 patients; however, patients with IgG4 autoantibody–positive CIDP have several clinically common characteristics. Given its mechanism of action, rituximab is likely to be effective in patients with IgG4 autoantibody (anti-CNTN1 and anti-NF155)–positive CIDP. Accordingly, we are planning to develop rituximab for use in these patients and present here the protocol for the exploratory study intended to secure approval of rituximab in Japan. We have attended a consultation meeting with the PMDA, which has agreed to the development strategy and initial design of the RECIPE trial.

### Conclusion

This article has described the design and protocol being used in the RECIPE trial. We outlined the characteristics of patients with IgG4 autoantibody–positive CIDP and discussed some critical considerations for these patients. The RECIPE trial is the first randomized controlled trial of rituximab for IgG4 autoantibody–positive CIDP. It is anticipated that the results will lead to a pathogenesis-oriented therapeutic strategy that can target specific phenotypes of CIDP and confirm the efficacy of rituximab in refractory IgG4 autoantibody–negative CIDP.

## Abbreviations

CASPR 1: contactin-associated protein 1.
CIDP: chronic inflammatory demyelinating polyradiculoneuropathy.
CNTN1: contactin-1.
EFNS/PNS: European Federation of Neurological Societies/Peripheral Nerve Society.
Ig: immunoglobulin.
INCAT: Inflammatory Neuropathy Cause and Treatment.
IVIg: intravenous immunoglobulin.
MuSK: muscle-specific tyrosine kinase.
NF155: neurofascin-155.
PMDA: Pharmaceuticals and Medical Device Agency.
